### Health-related quality of life (HRQoL)

Disease-specific quality of life is assessed using the SNOT-22, a widely recognized tool that measures the physical, functional, and emotional impacts of CRS. It is a reliable instrument for detecting changes related to interventions (21, 22). The minimal clinically important difference (MCID) for SNOT-22 is 8.9 points for surgically treated patients (21) and 12 points for medically treated patients (23).

General health-related quality of life (HRQoL) is evaluated using two self-administered questionnaires. The EQ-5D-5L assesses five domains: mobility, self-care, usual activities, pain/discomfort, and anxiety/depression (24). The index score ranges from 0 (poor health) to 1 (perfect health), and patients also rate their overall HRQoL using a visual analog scale (VAS), ranging from 0 (worst health) to 100 (best health). The 15D questionnaire, a validated HRQoL tool, measures 15 dimensions of health, including mobility, vision, hearing, breathing, sleep, eating, speech, excretion, daily activities, mental functioning, discomfort, depression, distress, vitality, and sexual activity (25). Respondents select one of five levels for each dimension (1 = best, 5 = worst). The 15D score reflects overall HRQoL, ranging from 0 (dead) to 1 (full health). MCID for the 15D score is ±0.015 (26).

### Olfactory function

Olfaction is assessed using the Sniffin' Sticks identification test, which consists of 12 pens, each containing a distinct common odor. During the test, one pen is placed under the nose for a few seconds at a time. After each presentation, the participant is asked to choose from four options. The forced-choice format is explained to the participant, as it may increase the likelihood of correct responses by chance. The total score is determined by the number of correct identifications out of the 12 odors presented. The MCID for the Sniffin' Sticks test is 5.5 points (27).

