### Subjects

The target number of participants for the study is 75 adult N-ERD patients with CRSwNP. This target was determined based on a power calculation, assuming a mean posttreatment difference of at least 13 in the sinonasal outcome test-22 (SNOT-22) between the treatment arms. In a previous study, the response within each subject group was normally distributed with a standard deviation of 17. To detect a true difference of 13 between the experimental and control means, we calculated that 42 experimental subjects and 21 control subjects would be needed to reject the null hypothesis that the population means are equal, with a power of 0.8 and a Type 1 error probability of 0.05. An estimated dropout rate of 15% was factored into this calculation, and if the dropout rate were higher, we would expect smaller effect sizes.

Had endoscopic sinus surgery been performed on 50% of the subjects prior to trial medication, the total number of participants required would have been 150. However, conducting the surgery before starting ATAD was not feasible due to the large number of subjects needed, given the limited number of N-ERD patients available for recruitment in the Hospital District of Helsinki and Uusimaa.

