### Secondary objectives

1.Assess the relative change in endoscopic nasal polyp score (NPS) between the two treatment groups at 11 months post-randomization.2.Assess the relative change in olfactory function and nasal patency measurements between the treatment groups.3.Assess the relative change in asthma-specific health-related quality of life (HRQoL), as measured by the asthma control test (ACT), among participants with asthma.4.Assess the relative change in lung function parameters and exhaled nitric oxide [fractional exhaled nitric oxide (FeNO)] between the treatment arms.5.Assess the relative change in Lund–Mackay (LM) scores on sinus CT scans between the two groups.6.Compare exacerbation rates, need for rescue treatments, work absences, overall costs, and safety outcomes between the treatment groups.7.Evaluate clinical parameters during ASA desensitization, including vital signs [ECG, forced expiratory volume in 1 s (FEV1), pulse, blood pressure], physical findings, reported symptoms, peak nasal inspiratory flow (PNIF), and adverse effects.8.Assess the frequency and nature of adverse effects associated with ATAD.9.Investigate changes in molecular markers and microbiome composition between the treatment groups.10.Identify biomarkers predictive of ATAD efficacy and safety.

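### The MCID of 5.5 points given for olfaction does not fit the 0–12 identification score it is attached to: a patient starting at 7 or more cannot reach it

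*Protocol article*

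**What the plan says.** The protocol article makes olfaction a secondary outcome. Under Secondary objectives, item 2 is to "Assess the relative change in olfactory function and nasal patency measurements between the treatment groups". The Abstract and the Primary and secondary outcomes section both name the Sniffin' Sticks identification test as the measure.

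The Olfactory function section describes that test and no other:

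- Items: "which consists of 12 pens, each containing a distinct common odor".
- Response format: "After each presentation, the participant is asked to choose from four options". The section notes of the forced choice that "it may increase the likelihood of correct responses by chance".
- Scoring: "The total score is determined by the number of correct identifications out of the 12 odors presented".
- Threshold: "Sticks test is 5.5 points (27", where 27 is the reference number.

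The threshold sentence names the Sniffin' Sticks test without the word identification. As no other component or longer scale is described anywhere in the article, a reader can only apply the 5.5 to the 0–12 count.

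**The concern.** An MCID is meant to mark the smallest change that matters to a patient. Here it is close to half the whole scale, and for part of the scale it lies beyond the best result the test can record. A patient who goes from 7 to a perfect 12 would count as not having changed by a clinically important amount.

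The article quotes an MCID for most of its outcome measures. It does not say how they will be used, but the natural use is in judging whether an observed effect matters. The Abstract lists loss of smell among the problems to which N-ERD patients are more prone, so the smell result will be looked at. If 5.5 is the value it is held against, a large real gain could be reported as falling below the MCID.

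**Working it through.** The 5.5 is a cited value with no inputs in the article, so it cannot be re-derived. It can be checked against the scale described beside it.

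**Inputs (Olfactory function section).** Items n = 12. Options per item = 4, so the guessing probability is p = 1/4. The score is an integer from 0 to 12. The stated MCID is 5.5.

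**Step 1: share of the scale.** 5.5 / 12 = 0.458, or 46% of the full range.

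**Step 2: smallest qualifying individual gain.** Scores are integers, so a gain of at least 5.5 means a gain of at least 6.

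**Step 3: ceiling.** The largest possible gain is 12 − baseline.

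| Baseline | Largest gain | Can reach 5.5? |
|---|---|---|
| 3 | 9 | yes, with a score of at least 9 |
| 5 | 7 | yes, with a score of at least 11 |
| 6 | 6 | only with a perfect 12 |
| 7 | 5 | no |
| 8 to 12 | 4 to 0 | no |

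**Step 4: chance level.** Mean under guessing = 12 × 1/4 = 3. SD = √(12 × 1/4 × 3/4) = 1.5. Measured from that mean, 5.5 is 5.5 / (12 − 3) = 61% of the distance to the maximum. This is only a descriptive figure, since 3 is an average and not a floor.

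**Step 5: group level.** A mean difference, unlike one patient's change, can equal 5.5. If the placebo mean at follow-up is 3, the active mean must be 3 + 5.5 = 8.5. If the placebo mean is above 12 − 5.5 = 6.5, no difference of 5.5 in follow-up means is possible.

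**Step 6: illustration for patients who start at chance.** Assume independent items with a common success probability, pure guessing at baseline, and a true mean of m out of 12 at follow-up. The exact binomial probability of an observed gain of at least 6 is:

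| True follow-up mean m | P(gain ≥ 6) |
|---|---|
| 7 | 26% |
| 8 | 42% |
| 9 | 61% |
| 10 | 78% |

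The threshold is demanding even where the ceiling does not bind, but it is not out of reach.

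**Step 7: comparison with the article's other MCIDs, where it gives both range and threshold.**

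| Measure (section) | MCID / range | Share |
|---|---|---|
| 15D (Health-related quality of life) | 0.015 / 1 | 1.5% |
| Nasal polyp score (Nasal endoscopy) | 1 / 8 | 12.5% |
| Asthma control test (Asthma control) | 3 / (25 − 5) | 15% |
| Sniffin' Sticks (Olfactory function) | 5.5 / 12 | 46% |

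The olfactory value is about three times the next largest (46 / 15 ≈ 3.1).

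**The case against.** The strongest reply is that nothing in the article uses 5.5. Secondary objective 2 compares change between groups, the Primary and secondary outcomes section lists changes, and the Statistical methods section describes ANCOVA and linear mixed models without mentioning any MCID or responder rule. On this view the figure is a background citation in an instrument description. That stands as far as the planned between-arm comparison goes: the comparison is unaffected, and no change to the analysis model is needed.

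Three further points also stand.

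- A non-integer MCID is not in itself an error. A group mean can move by 5.5; only an individual cannot.
- The chance score of 3 is a mean. A pure guesser scores 0 to 2 about 39% of the time (binomial, 12 items, probability 1/4), so the 46% of the full range is the firm figure and the 61% is a convention.
- Reference 27 is not at hand, so it cannot be said that its authors derived 5.5 on a different version of the test, nor what value should replace it.

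A reader might infer that smell benefit will nearly always be judged unimportant whatever aspirin does. The article does not support that. It gives no baseline smell scores, and its inclusion criteria select severe disease, so many patients may start low, where the ceiling does not bind. The illustration above also shows a patient moving from guessing to a true mean of 9 meeting the threshold 61% of the time.

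What the reply does not remove is the mismatch itself. The article prints a specific threshold next to a scale it does not fit, and this is not a detail left to a fuller document.

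**Conclusion.** The point holds as an error in a stated interpretive threshold for one secondary outcome. It rests only on the test description in the Olfactory function section and on reading the 5.5 as applying to the one test described there. The ceiling result needs no distributional assumption; only the probabilities in Step 6 do.

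Its reach is limited. The primary endpoint, the sample size and the data are untouched. How many trial patients start at 7 or more is unknown, so the practical effect on this trial cannot be sized from the article.

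Correction is still worthwhile. It is cheap, and it prevents a substantial gain, such as 7 to 12, from being described as below the minimal important difference.

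**What to change.** - Do not apply 5.5 points to the 12-item identification score.
- Check which Sniffin' Sticks version and scale reference 27 used.
- Before interpreting the smell results, either state a threshold shown to be valid for the 12-item identification score, with its source, or say that none is available.
- In either case, report the between-arm mean difference on the 0–12 score with its 95% CI, so that readers can judge its size directly.

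The cost is one look at a cited source and one sentence in the outcome description. It needs no new data and no change to the planned comparison. The Trial status section says that the data are now being analysed, so the correction should be made and dated before the smell results are written up.

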### Nasal patency

Nasal patency is assessed using the peak nasal inspiratory flow (PNIF) method with a portable GMI PNIF meter (GM Instruments). A ventilation mask is securely placed over the nose, and the patient is instructed to close their mouth and inhale as forcefully as possible through the nose. The highest inspiratory flow from three maximal inhalations is recorded for analysis. The MCID for PNIF is approximately 20 L per minute (28).

Acoustic rhinometry is used to estimate the cross-sectional diameter of the nasal cavity at various points, with minimal cross-sectional areas recorded. This test is performed after a 15–20 min acclimatization period to allow the patient to adjust to the room's temperature and humidity. A trained nurse or doctor conducts the measurements.

### Lung function

Spirometry is performed at recruitment and at the cessation of medication. It is also conducted if there is suspicion of uncontrolled asthma. The minimal clinically important difference (MCID) for forced expiratory volume in 1 s (FEV_1_) in asthma is considered to be 11% (29).

Mini-spirometry (FEV_1_) is performed on the ASA desensitization days before the first dose, before the second dose, and after the second dose.

Peak expiratory flow (PEF) is measured by patients at home over one week at four timepoints: during recruitment, before ASA desensitization, at discontinuation of medication, and before the end of the trial. The MCID for PEF is an improvement of 12%, as suggested by a study on asthma patients (30).

Fractional exhaled nitric oxide (FeNO) measures airway inflammation, primarily in asthma, reflecting eosinophilic activity and disease control. The MCID for FeNO is a relative change of ≥20% (31).

### Nasal endoscopy

The modified Lund endoscopy score (32) is used to assess polyps, edema, and discharge, with scores ranging from 0 to 2 (33). Polyps are further evaluated using the modified Davos scale, which ranges from 0 to 4 on each side (34):
*Score 0*: no polyps*Score 1*: small polyps in the middle meatus, not extending below the inferior border of the middle turbinate*Score 2*: polyps in the middle meatus extending below the inferior border of the middle turbinate*Score 3*: polyps below the lower border of the middle turbinate, with large medial polyps or any polyp reaching the lower border of the inferior turbinate*Score 4*: polyps extending below the lower border of the inferior turbinate (35).

The total score (0–8) is calculated by summing the scores for both sides. The MCID for the nasal polyp score (NPS) is 1 point (3, 4).

### CRS disease control

The criteria for assessing clinical control of CRS are outlined in the EPOS guidelines from 2012–2020 (3, 18). Disease control is determined by evaluating common nasal symptoms, sleep disturbances, or fatigue, alongside endoscopic findings and the need for systemic corticosteroids or long-term antibiotics within the past 1 or 3 months (18, 36). Symptom control is defined as a state where patients either have no symptoms or the symptoms are not disruptive. The MCID for overall CRS control has not been universally agreed upon in the guidelines.

### Asthma control

Asthma control is assessed using the asthma control test (ACT) (37) and the Mini Asthma Quality of Life Questionnaire (Mini AQLQ) (38). The ACT evaluates the frequency of shortness of breath, general asthma symptoms, use of rescue medications, the impact of asthma on daily activities, and overall asthma control. Symptoms and activities are rated on a five-point scale, 1 = all the time to 5 = not at all, and for asthma control, 1 = not controlled at all to 5 = completely controlled. Scores range from 5 (poor asthma control) to 25 (complete control), with higher scores indicating better asthma control. A score above 19 suggests well-controlled asthma. The Mini AQLQ consists of 15 questions, covering the same domains as the original AQLQ (symptoms, activities, emotions, and environment). The MCID for the AQLQ is a change of >0.5 (39), and the MCID for the ACT is 3 points (40).

### Exacerbations

Exacerbations of upper or lower airway symptoms requiring increased medication, emergency or outpatient visits, hospitalization, and reduced productivity and sick leave, are documented for the year prior to ASA desensitization and during each follow-up visit over the 12-month follow-up period.

### Productivity, health resource use, and costs

Patients report impaired activity and productivity using the Work Productivity and Activity Impairment Questionnaire (WPAI: GH) (41). Healthcare resource utilization, including medical costs, healthcare services, and productivity costs, is collected from hospital databases, intervention reports, medical records, and national health records. These data are also gathered using the Productivity COST Questionnaire (iPCQ) and the Medical Consumption Questionnaire (iMCQ) (42).

### Adverse effects and safety

Adverse effects related to CRS and asthma treatment in the year prior to enrollment, as well as at each visit and follow-up call during the 12-month period, are documented. Participants are encouraged to contact the investigators whenever needed. Side effects of the investigational medicinal product (IMP) are recorded throughout the follow-up. Any unexpected or sudden adverse effects during the trial are documented in accordance with the 2017 updated Guideline for Good Clinical Practice (GCP) (EMA/CPMP/ICH/135/95). Adherence to the IMP is monitored at each visit through interviews with the study nurse and investigator.

### Tissue and mucus samples

Nasal mucus, epithelial, and polyp tissue samples are collected before randomization and at 5 and 11 months after starting the IMP to examine molecular and cellular changes, as well as microbiome and transcriptome profiles related to efficacy and safety. Participants are also invited to voluntarily donate a blood sample to the Finnish National Biobank for inclusion in a nationwide genome-wide association study (GWAS) project. (https://www.finngen.fi/en).

### Data collection, management, and storage

Clinical data are obtained from electronic patient records, while study information is collected using paper questionnaires. These paper questionnaires, measurement results, and signed informed consent forms are securely stored in locked cabinets. The data are then transferred to electronic case report forms for analysis, stored within a system provided to Helsinki University Hospital by Granitics Ltd., Espoo, Finland.

### Statistical methods

The primary objective of the study is to evaluate the improvement in key endpoints, including the change from baseline to 1 year after starting ATAD, in SNOT-22 scores and the endoscopic nasal polyp (NP) score. Power calculations and randomization procedures for these primary endpoints have been previously outlined. An additional secondary endpoint is the change from baseline in FEV1 at 1 year. The analysis of each imputed complete datapoint will be conducted using an analysis of covariance (ANCOVA) model, linear mixed models, incorporating baseline values, treatment group, prior surgery history, sex, age, and region as covariates. Missing data will be addressed through multiple imputation, and sensitivity analyses will be performed to assess the robustness of the results.

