**Methods:**

AirGOs Medical is an investigator-initiated RDBCT conducted at Helsinki University Hospital. Participants are randomized to receive either ATAD or placebo. The primary endpoint is the change in the SNOT-22 score observed at the 11-month follow-up. Secondary measures include variations in nasal polyp scores, CRS symptom control, general HRQoL, work productivity loss, peak nasal inspiratory flow (PNIF) with or without acoustic rhinometry (ARM), olfactory function assessed by the Sniffin' Sticks identification test, spirometry, peak expiratory flow (PEF), and histopathological findings at the 12-month follow-up.

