### Primary objective

The primary objective of this study is to assess the relative change in a validated quality of life measure, the sinonasal outcome test-22 (SNOT-22), from baseline to 11-month follow-up between the two randomized treatment arms, i.e., (i) 250 mg Primaspan tablet once daily and (ii) placebo tablet once daily, in patients diagnosed with CRSwNP and N-ERD.

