### Follow-up

Patients are followed up at 1, 5, 11, and 12 months after randomization. A detailed overview of the follow-up procedures and assessments is presented in Figure 1.

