## Results

### Primary and secondary outcomes

The primary outcome is the change in the SNOT-22 score at the 11-month follow-up. Secondary outcomes include changes in the endoscopic nasal polyp score (NPS), LM CT score, HRQoL, loss of productivity, nasal patency [peak nasal inspiratory flow (PNIF) ± acoustic rhinometry (ARM)], olfaction (Sniffin' Sticks identification test), lung function (spirometry, exhaled NO, and PEF), and pathological findings at the 12/24-month follow-up (Figure 1). Safety assessments, including complications and adverse effects, as well as costs and loss of productivity, will be compared between the treatment arms. Additionally, the costs of CRSwNP and asthma treatment 1 year before and 1 year after randomization will be compared by treatment arm. All outcome measurements will be conducted by trained study nurses and investigators. Physiological tests will be performed by a study nurse under the supervision of an investigator and a pulmonologist. Laboratory tests, including skin prick tests, blood tests, and tissue eosinophilia, will be conducted in accredited university hospital laboratories.

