Targeted biologic therapies have significantly advanced the treatment of Type 2 inflammatory diseases, including N-ERD (48). These therapies are typically considered alongside other advanced options, such as endoscopic sinus surgery and ATAD. The efficacy and safety of biologics for N-ERD patients have been demonstrated in several studies (49). Biologic therapies are recommended for patients who cannot tolerate ASA due to conditions such as gastritis, bleeding risks, or severe uncontrolled asthma (50). However, some patients may require long-term ASA or NSAIDs for other conditions, such as cardiovascular disease, making ASA desensitization a potential option for these individuals (51). To the authors' knowledge, there are no available results from RDBCT studies directly comparing ATAD with biological therapies.

Our randomized double-blind controlled clinical trial assesses the safety and efficacy of ATAD in treating patients with CRSwNP and N-ERD. We will monitor general and disease-specific HRQoL, disease control in CRS and asthma, olfactory function, endoscopic nasal polyp score, lung function, absenteeism, and decreased productivity at work, as well as treatment resource utilization. Adverse events related to the treatments will be monitored throughout the study. Participants first undergo the 4-day desensitization phase and then continue to 11-month maintenance treatment with either aspirin or placebo. Several control visits with doctors during the study will monitor adverse events, disease control, and other factors. After cessation of medication, a posttreatment visit will take place 1 month after stopping the medication. We acknowledge that the study is limited to a single hospital district, which may affect its external validity. Additionally, we recognize that the lack of a direct comparison to biological therapies limits the study's broader impact.

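### The statistical methods time the primary SNOT-22 change at 1 year after starting ATAD, but the objective and outcome sections time it at the 11-month visit; read literally, the 1-year value is post-treatment

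*Protocol article*

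**What the plan says.** Three places in the protocol article agree on the primary timepoint:

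- Abstract, Methods: "The primary endpoint is the change in the SNOT-22 score observed at the 11-month follow-up".
- Primary objective: the change is assessed "from baseline to 11-month follow-up between the two randomized treatment arms".
- Primary and secondary outcomes: "The primary outcome is the change in the SNOT-22 score at the 11-month follow-up".

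The Statistical methods section, the only text on how SNOT-22 will be analysed, states the primary objective differently: "the change from baseline to 1 year after starting ATAD, in SNOT-22 scores". It does not say that this means the 11-month visit.

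The schedule keeps the two times apart. Under Follow-up: "Patients are followed up at 1, 5, 11, and 12 months after randomization". The Discussion says that participants "continue to 11-month maintenance treatment with either aspirin or placebo" and that "a posttreatment visit will take place 1 month after stopping the medication".

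**The concern.** The two visits differ in treatment status, so the gap is more than one month of calendar time. Month 11 closes the randomized treatment. Month 12 comes after a month without it. A between-arm difference at month 11 estimates the effect at the end of treatment; at month 12 it estimates what is left after withdrawal. These are different questions, and the article assigns both to the primary analysis.

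The Trial status section says the trial ran from 2019 to 2023 and that the data are being analysed. While two primary timepoints stand in the published plan, either can be presented as the prespecified one, and a reader cannot tell whether the choice was made before the results were seen.

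**Working it through.** **Step 1. Do the two times fall at the same visit?**

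- Follow-up lists months 11 and 12 as separate visits, counted from randomization.
- Maintenance lasts 11 months and the last visit comes 1 month after stopping (both Discussion): 11 + 1 = 12. The 12-month visit is therefore the post-treatment visit.
- ATAD begins with a 4-day desensitization before randomization (ASA desensitization before randomization), and the Discussion describes maintenance as following on from it. One year after starting therefore falls nearest month 12, whether counted from desensitization or from the first maintenance dose. For it to coincide with month 11, about a month would have to pass between desensitization and randomization, and the article states no such interval.

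Taken at its word, the Statistical methods text points to the post-treatment visit.

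**Step 2. Does the sample-size text decide between them?**

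The Subjects section sizes the trial by "assuming a mean posttreatment difference of at least 13 in the sinonasal outcome test-22 (SNOT-22) between the treatment arms". It names no visit and no on-treatment condition. The Discussion uses the same adjective for the visit after stopping. The section does not settle the matter.

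**Step 3. Reproduce the plan's sample size.**

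Inputs (Subjects; ratio from Randomization): difference 13, SD 17, alpha 0.05, power 0.80, 2:1 allocation, 15% dropout.

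- Control n = (1 + 1/2) × (1.960 + 0.842)² × 17² / 13² = 1.5 × 7.85 × 1.710 = 20.1, rounded up to 21. Experimental n = 2 × 21 = 42.
- Total 63; 63 / 0.85 = 74.1, rounded up to 75.
- The one-sided version gives 16 and 32, which does not match, so the calculation is two-sided.

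The plan's 42, 21 and 75 reproduce. Since no visit enters the formula, choosing either visit changes none of them.

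**Step 4. Illustration of sensitivity to the visit.**

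The documents give no figure for how much effect remains a month after stopping, so the retained share is an assumption and is shown as a range. It also assumes that the 13 points apply at month 11.

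Standard error = 17 × √(1/21 + 1/42) = 17 × 0.2673 = 4.543. Noncentrality = difference / 4.543. Power is from the two-sided noncentral t with 61 degrees of freedom.

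| Share of 13 points retained | Difference | Noncentrality | Power |
|---|---|---|---|
| 100% | 13.0 | 2.861 | 0.80 |
| 90% | 11.7 | 2.575 | 0.72 |
| 75% | 9.75 | 2.146 | 0.56 |
| 50% | 6.5 | 1.431 | 0.29 |

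**The case against.** The best reply is that the 1-year wording is loose phrasing for the end-of-treatment visit. Three dedicated endpoint statements name 11 months. The Statistical methods also call FEV1 a 1-year endpoint, while the Lung function section schedules routine spirometry only at recruitment and when medication stops, which is month 11. Timing is loose elsewhere too: the polyp score is placed at 11 months in the secondary objectives, at 12 months in the abstract and at 1 year in the Statistical methods. This reading is plausible and cannot be excluded. It is not conclusive, because the abstract lists spirometry among the 12-month measures. Even if it is right, the sentence that governs the primary analysis has not been aligned with the visit schedule.

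A second reply is that no visible text confirms SNOT-22 collection at month 12, since the assessments per visit are in Figure 1, which is not shown. That stands. If SNOT-22 is not collected then, the off-treatment test could not be run, but the Statistical methods would name a time without primary data and would still need correction.

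Stronger claims are tempting but unsupported:

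- A reader might infer that the primary test will be run off treatment. That is one of two readings.
- A reader might take the 24–72 h refractory period in the Introduction as evidence that benefit is lost within a month. That figure describes the post-dose window used for desensitization. It says nothing about how long a SNOT-22 benefit lasts after 11 months of daily treatment.
- A reader might say that the 1-year reading dilutes the effect the trial was powered for. The Subjects section does not tie the 13 points to month 11 or to being on treatment.

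**Conclusion.** The contradiction is real and concerns the visit of the primary test. Three statements give month 11; the analysis text gives 1 year, which on the article's own schedule is closest to a post-treatment visit. This is not a detail left to an analysis plan: the article states the timepoint, in two incompatible ways.

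This is an error in the definition of the endpoint and not a numerical one. The sample size reproduces and is unaffected. No loss of power is established. The range from 0.80 down to 0.29 rests on assumed retention from 100% to 50% and on month-12 SNOT-22 data existing. What is established is that the primary analysis has two written timepoints while the data are being analysed.

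**What to change.** Amend the Statistical methods sentence so that the primary SNOT-22 analysis uses the change from baseline to the 11-month visit, in line with the abstract, the primary objective and the outcomes section. If SNOT-22 is also collected at month 12, label that analysis as secondary and post-treatment.

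Do this before the code is broken. The Randomization section allows the envelopes to be opened only after the monitor's closure visit and with permission; the article does not say whether this has happened. If it has, document from records that predate unblinding which visit was prespecified, and report the results at both visits.

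The cost is one sentence, plus a short audit of records if the blind is already open. No new patients or measurements are needed, and 42 + 21 (75 with dropout) stays. The amendment does not settle whether change is relative or in points, or whether the polyp score is also primary; those are separate questions.

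### Statistical methods counts the nasal polyp score as a second primary endpoint and says it was powered, but elsewhere it is secondary and only SNOT-22 has a power calculation

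*Protocol article*

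**What the plan says.** Four parts of the Protocol article agree on the status of the endpoints:

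- The Abstract (Methods) names one primary endpoint, SNOT-22 change at 11 months, and puts nasal polyp scores among the secondary measures.
- Primary objective names SNOT-22 only.
- Secondary objectives, item 1, reads: "Assess the relative change in endoscopic nasal polyp score (NPS) between the two treatment groups at 11 months post-randomization".
- Primary and secondary outcomes again names SNOT-22 as the primary outcome and lists NPS as secondary.

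Statistical methods differs. It describes the primary objective as improvement in a set of key endpoints, given as change "in SNOT-22 scores and the endoscopic nasal polyp (NP) score". Its next sentence is "Power calculations and randomization procedures for these primary endpoints have been previously outlined".

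The calculation it points back to is under Subjects and concerns a SNOT-22 difference of 13 points. Its result is "we calculated that 42 experimental subjects and 21 control subjects would be needed", and the error rates behind it are given as "with a power of 0.8 and a Type 1 error probability of 0.05". The SD is also that of SNOT-22: "the response within each subject group was normally distributed with a standard deviation of 17". No design difference, SD or power for NPS appears anywhere. The Nasal endoscopy section gives only a minimal clinically important difference of 1 point.

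**The concern.** The section that governs the analysis contradicts the objectives and outcomes sections on which endpoints are primary. It also refers to a power calculation for NPS that the article does not contain. Both are statements on the page, not details left to another document.

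What is at stake is which result may be reported as the trial's primary finding. Trial status says the trial ran from 2019 to 2023 and the data are being analysed. With two published definitions of the primary endpoint, a favourable result on either measure could be presented as the primary success. A reader could also take the 80% power figure to cover NPS, which it does not.

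**Working it through.** **1. Reproduce the stated sample size (SNOT-22).** Inputs from Subjects: difference 13, SD 17, alpha 0.05, power 0.8. Allocation 2:1 from Randomization. Sidedness is not stated; two-sided is assumed.

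Control n = (1 + 1/2) × (1.960 + 0.842)² × 17²/13² = 1.5 × 7.85 × 1.710 = 20.1, rounded up to 21. The ASA arm is 2 × 21 = 42, total 63. With 15% dropout, 63/0.85 = 74.1, rounded up to 75. Both match the article, including "The target number of participants for the study is 75 adult N-ERD patients with CRSwNP". A one-sided test would give 16 + 32, so the calculation was two-sided.

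Power at 42 + 21: standard error = 17 × √(1/42 + 1/21) = 4.54, and 13/4.54 = 2.86. Power = Φ(2.86 − 1.96) = 81.6% (normal), or 80.4% (noncentral t). With SNOT-22 as sole primary, the stated 5% and 80% both hold.

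**2. What 42 + 21 offers NPS.** At two-sided 0.05, 80% power needs a standardized effect of 2.80 × √(1/42 + 1/21) = 0.75. The article gives no NPS SD, so a range is assumed for a 1-point difference (noncentral t):

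| Assumed SD of NPS | Power |
|---|---|
| 1.0 | 96% |
| 1.3 | 81% |
| 1.5 | 69% |
| 2.0 | 45% |
| 2.5 | 31% |

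Power reaches 80% only if the SD is about 1.3 or less. It is unknown, not shown to be low.

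**3. What two primaries would mean.** The article states no success rule, so each of three is worked through. The correlation between the two test statistics is assumed.

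*Either endpoint suffices, 0.05 each.* Independent tests: 1 − 0.95² = 9.75%. Bivariate normal: 9.1% at correlation 0.5 and 8.3% at 0.7. The upper bound is 10%. SNOT-22 power is unchanged.

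*Both must succeed, 0.05 each.* The error rate stays at or below 5%. If NPS has the same standardized effect as SNOT-22, joint power is 0.816² = 0.67 at correlation 0, 0.71 at 0.5 and 0.73 at 0.7. It depends on the unknown NPS power: with independent tests, SD 1.0 gives 0.804 × 0.957 = 0.77, and SD 2.5 gives 0.804 × 0.313 = 0.25.

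*Bonferroni, 0.025 each.* The error rate holds. SNOT-22 power is Φ(2.86 − 2.24) = 73.2% (normal) or 71.3% (noncentral t). Restoring 80% takes 50 + 25 = 75 evaluable (normal) or 52 + 26 = 78 (t). That is 75/0.85 = 88.2, so 89 enrolled, or 78/0.85 = 91.8, so 92, against a target of 75.

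**The case against.** The best reply is that the intended primary endpoint can be recovered. The Abstract, Primary objective and outcomes section all name SNOT-22 alone, and the only power calculation belongs to it. One paragraph is loosely worded, and a success rule or alpha allocation may sit in a full protocol or analysis plan that is not shown.

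Much of this stands, and it rules out four stronger readings that a reader might reach:

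- **That the 5% error rate and 80% power do not hold.** They reproduce exactly for SNOT-22 as sole primary. Even with two primaries, none of the three rules worked through breaks both.
- **That NPS is underpowered.** With no SD or design difference given, the supported statement is only that its power is not established.
- **That the missing alpha rule is itself a defect.** An article commonly leaves this to the full documents.
- **That 11 months and 1 year for each endpoint make four primary tests.** Statistical methods does say 1 year where other sections say 11 months, but nowhere is confirmatory testing at both times proposed, and no correlations are given. That wording is a separate question, and no error rate is claimed for it here.

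The reply does not remove the contradiction. A plan held elsewhere cannot make this paragraph agree with the rest of the article, or supply the NPS calculation it says was already outlined. Nor is the pairing of the two measures wholly isolated: the hypothesis in the Introduction also names quality of life and polyp size together, though without giving either a rank.

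**Conclusion.** The concern holds as an internal contradiction and an incorrect back-reference in Statistical methods. NPS is called primary there and secondary in the Abstract, Secondary objectives and the outcomes section, and the power calculation said to cover it does not exist in the article.

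The consequence is conditional. With SNOT-22 as sole primary, nothing in the stated error rate or power changes. If Statistical methods were followed literally, the cost would depend on the rule: family-wise error of about 8–10%, or joint power of about 0.67–0.73, or SNOT-22 power of about 0.71–0.73. These figures assume two-sided tests at 42 + 21 evaluable. The first two also assume correlations of 0 to 0.7, and the joint-power range assumes that NPS has the same standardized effect as SNOT-22.

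**What to change.** In Statistical methods, name SNOT-22 change at 11 months as the sole primary endpoint at two-sided 0.05, list NPS as a secondary endpoint, and limit the power sentence to SNOT-22. Because the data are already being analysed, record the date of the correction and whether it came before or after the randomization codes were opened.

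Testing NPS in fixed sequence after SNOT-22 is optional. The correction does not need it. If adopted now, it would be a new confirmatory rule that needs its own justification and date.

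If the sponsor did intend NPS to be primary, the other sections must be changed to match, the success rule and its alpha stated, and an NPS power calculation supplied.

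The recommended correction is wording only and costs SNOT-22 no power or sample size. The downside is that an NPS result could not be presented as a primary success.
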